#### **Secondary outcomes**

Descriptive statistics will be calculated for all patients and reported with respect to each time point. Adequate GLM models will be used to compare groups with respect to clinic characteristics, therapeutic outcomes (PPI specific and other medication), Quality of life (EQ-5D-5L), BMQ specific applied to PPI, Adherence (MTA) and healthcare resource utilization. Changes over time points will be evaluated.

Patients' level of satisfaction and process outcomes will be analyzed only for the intervention arm. Process outcomes will be used to assess the fidelity and quality of the collaborative intervention.

Time to PPI discontinuation will be accessed through Kaplan-Meier (KM) estimator. Results will be stratified by group and KM curves will be presented. Log-rank test will be computed to compare results between cohort subgroups. If groups are unbalanced with respect to potential confounders, multivariate Cox Proportional Hazards models will be used instead. Univariate and multivariate hazard ratios (HR) will be computed, and Wald's 95% CI presented. Patients will be censored in the survival

analysis if they were lost to follow-up (subjects who could not be reached by telephone interview, or the primary outcome could not be computed or withdrew consent), hospitalized or died.

#### **6.15.3. Enrolled population and refusing subjects.**

Screening data will be collected on the population of pharmacies and patients invited to participate in this study. We will report:

- a) the total number of pharmacies in the study area, the total number of eligible pharmacies invited to participate, the total number of pharmacies who accept to participate and frequency of reasons for refusal if available. We will compare pharmacy characteristics (number of staff, rural/urban, volume of dispenses) of participating and non-participating pharmacies and test for significant differences using chi-square test for contingency tables.
- b) the total number of patients invited to participate, the total number of patients who accept to participate and frequency of reasons for refusal if available. Age (group), gender, household dimension and higher educational level completed of the patients who are invited and refuse to be included in the study and of the patients enrolled will be tested for significant differences using chi-square test for contingency tables.

#### **6.15.4. Population of analysis**

Primary analysis will only consider patients for which a 6-month reported PPI use is available (here the definition of a complete case), assuming the reports are missing at random (MAR) if not available. Nevertheless, MAR assumption will be tested comparing patients with missing 6-month information regarding primary outcome with the remainder sample of patients with respect to the baseline characteristics.

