### **6.7. Study Follow-up**

Study follow-ups include 2 telephone calls, and electronic data extraction from the pharmacies dispense software at 3- and 6-months post recruitment. Telephone interviews are expected to last 10-15 minutes.

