#### **6.11. Sample size**

Our principal hypothesis is that our intervention will reduce the use of inappropriate PPIs compared to usual care.

Our assumption is that the intervention will reach a rate of discontinuation similar with that achieved in previous studies reporting medication withdrawals in intervention with collaborative work between pharmacists and GP, compared to usual care (minimum absolute difference of 20%)(79,97). Alongside,

we will also assume that a small rate of discontinuation will be observed in the group without the intervention (control Group) as much as of 10%.

Therefore, our study will be conducted to detect a minimal 20% increase in the rate of discontinuation of inappropriate medication use caused by the intervention compared with the usual care. Assuming an alpha of 5%, 90% power and an allocation ratio of 1:1, we estimate that the minimum total sample size to detect differences between intervention and control group is 178 patients (89 patients per group).

Considering a 20% lost to follow-up, then a total of 222 patients (111 per group) recruited in the participating pharmacies will be needed in this study.

The sample size was calculated using the software G\*Power version 3.1.9.6.

**Exact** - Proportions: Inequality, two independent groups (Fisher's exact test)

**Options:** Exact distribution

**Analysis:** A priori: Compute required sample size

|                |                             |   |           |
|----------------|-----------------------------|---|-----------|
| Input:  | Tail(s)                     | = | Two       |
|                | Proportion p1               | = | 0.1       |
|                | Proportion p2               | = | 0.3       |
|                | $\alpha$ err prob           | = | 0.05      |
|                | Power (1- $\beta$ err prob) | = | 0.90      |
|                | Allocation ratio N2/N1      | = | 1         |
| Output: | Sample size group 1         | = | 89        |
|                | Sample size group 2         | = | 89        |
|                | Total sample size           | = | 178       |
|                | Actual power                | = | 0.9017447 |
|                | Actual $\alpha$             | = | 0.0340267 |

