### **6.15.2. Study outcomes**

An intention-to-treat population will be considered, including patients regardless to the degree to which they have been exposed to the intervention (as this is a pragmatic trial). Outcomes will be estimated for the whole dataset. 95% confidence intervals will be reported.

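### The primary analysis is complete-case (6.15.4) although the protocol states intention-to-treat on the whole dataset (6.15.2), and the planned baseline comparison cannot test MAR

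*Protocol*

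**What the plan says.** **Population.** Protocol 6.15.2 reads: "An intention-to-treat population will be considered, including patients regardless to the degree to which they have been exposed to the intervention". It adds that outcomes will be estimated on the full dataset, and the Protocol Summary repeats both statements. Section 6.15.4 then fixes the primary set: "Primary analysis will only consider patients for which a 6-month reported PPI use is available (here the definition of a complete case"). Missing reports are taken to be MAR.

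**Check of the assumption.** Section 6.15.4 continues: "MAR assumption will be tested comparing patients with missing 6-month information regarding primary outcome with the remainder sample of patients", with respect to baseline characteristics. Section 7 plans a further baseline comparison of dropouts, by arm.

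**Outcome data.** Section 6.8 ascertains the primary outcome from pharmacy sales linked to the patient's tax number (NIF) and confirms it by self-report. It defines discontinuation through reported non-use or reported dose reduction. Follow-up consists of research-team telephone calls plus "electronic data extraction from the pharmacies dispense software at 3- and 6-months post recruitment" (6.7). Table 4 schedules PPI outcomes at 3 and 6 months.

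**Survival analysis (secondary).** Section 6.15.2 censors patients who could not be reached by telephone, "or the primary outcome could not be computed or withdrew consent), hospitalized or died".

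**The concern.** The protocol gives two answers to the question of who is in the primary analysis. One is everyone, by arm. The other is only those with a 6-month report. Section 6.11 expects one patient in five to be lost, so the choice can move the headline risk difference, the number needed to treat, and the cost-effectiveness ratio built on the same outcome (6.17.4.1).

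The safeguard does not do what it claims. MAR says that, given the observed data, missingness does not depend on the unobserved 6-month value. Comparing baseline characteristics of patients with and without that value says nothing about the value itself. A clean comparison could be read as support for the complete-case result when it is not. The rule also sets aside 3-month PPI status, which will be known for some patients without a 6-month report and is likely to be the best predictor of it.

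**Working it through.** **1. Planning figures (6.11).** The inputs are "Assuming an alpha of 5%, 90% power and an allocation ratio of 1:1", a two-sided Fisher's exact test, and 10% in controls versus 30% in the intervention arm. Exact enumeration at 89 per arm gives power 0.9017447, the stated value; 88 per arm gives 0.8977. Loss: 178/0.8 = 222.5, stated as 222 (111 per arm), and 0.8 × 111 = 88.8. The sample size therefore reproduces, and it provides for about 89 completers per arm.

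**2. Effect of the missing patients.** The documents give no outcome rates for missing patients, so those below are assumptions. Completers are set at the planned 10% and 30%. In each arm:

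rate in all enrolled = completer rate × (1 − d) + rate in the missing × d, where d is the fraction missing.

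'On PPI' means counted as neither stopped nor reduced.

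| Assumption | Control | Intervention | Difference (points) | NNT |
|---|---|---|---|---|
| 20% missing per arm, missing like completers of their arm (MAR) | 10% | 30% | 20 | 5.0 |
| 20% per arm, all missing on PPI | 0.8 × 10 = 8% | 0.8 × 30 = 24% | 16 | 6.25 |
| 20% per arm, missing at 10% in both arms | 8 + 2 = 10% | 24 + 2 = 26% | 16 | 6.25 |
| 20% per arm, only missing intervention patients on PPI | 10% | 24% | 14 | 7.1 |
| 20% per arm, only missing controls on PPI | 8% | 30% | 22 | 4.5 |
| 30% intervention, 10% control missing, all on PPI | 0.9 × 10 = 9% | 0.7 × 30 = 21% | 12 | 8.3 |
| 10% intervention, 30% control missing, all on PPI | 0.7 × 10 = 7% | 0.9 × 30 = 27% | 20 | 5.0 |

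The extreme bounds at 20% missing per arm are 24 − (8 + 20) = −4 and (24 + 20) − 8 = +36 points. The complete-case figure is 20 points in every row.

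**3. Power with all enrolled patients.** At 8% versus 24% with 111 per arm, Fisher's exact test has power 0.887; 116 per arm would give 0.90.

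**4. Censoring at hospitalisation (secondary outcome).** Assume 10% of patients are hospitalised uniformly over 6 months and never stop, and a fraction p of the rest stop uniformly over months 0 to 3. True cumulative discontinuation is 0.9p. The hazard that Kaplan-Meier sees is 0.3p / [1 − (0.3p + 0.1/6)t] for t up to 3 months.

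- p = 30%: hazard 0.09/(1 − 0.10667t). The integral is (0.09/0.10667) × −ln(0.68) = 0.325, so 1 − KM = 27.8% against a true 27.0%, or +0.8 points.
- p = 10%: hazard 0.03/(1 − 0.04667t). The integral is (0.03/0.04667) × −ln(0.86) = 0.097, so 1 − KM = 9.2% against a true 9.0%, or +0.2 points.

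The between-arm inflation in this example is about 0.5 points.

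**The case against.** **The intention-to-treat wording concerns exposure.** Section 6.15.2 defines it by not excluding patients for incomplete exposure to the intervention, and 6.15.4 leaves that intact. One could read the plan as analysis by arm among those with data. The statement that outcomes are estimated on all the data does not fit that reading, so the conflict stands.

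**The primary model is covariate-adjusted.** With only the outcome missing, an adjusted complete-case model is valid if missingness depends only on arm and the covariates in the model. This is correct. It means complete-case analysis need not be biased, but the baseline comparison still cannot show that the condition holds.

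**Missing-data detail belongs to the SAP.** In general it does, and the absence of an imputation model here is no fault. The primary set and the claim to test MAR, however, are fixed in the protocol itself.

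A reader might also infer stronger points that the documents do not support:

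- *That the effect will be overstated.* One can argue that intervention patients still on a PPI avoid the interviewer, but nothing in the documents establishes this. Control non-response could be the higher, and the table contains rows with no change and one in the opposite direction.
- *That non-responders can simply be classified from dispensing records.* Section 6.8 requires confirmation by report, and an absent sale may be a purchase elsewhere. Section 6.11 puts about 94% of PPI sales prescribed by the two intervention units in the selected pharmacies. It gives no such figure for controls, where 6.1 expects about 20% of pharmacies to join. Misclassification would probably differ by arm.
- *That the censoring rule breaches intention-to-treat.* It does not: patients stay in their arm until censored, and only a secondary outcome is affected.
- *That the censoring rule cannot be carried out because Table 5 lists no admission or death date.* The 6-month questionnaire (Annex 14) is not shown, so this cannot be settled.

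**Conclusion.** The point holds in limited form. Sections 6.15.2 and 6.15.4 contradict each other on the primary analysis population, and the statement that MAR will be tested is wrong in principle. With 20% loss per arm and completers at the planned rates, the difference lies between 14 and 20 points across the main scenarios (all missing patients on PPI, only the missing intervention patients on PPI, or MAR). It falls to 12 if loss is 30% versus 10% and all missing patients are on PPI. All of this rests on assumed outcomes in missing patients, so the table shows sensitivity and does not estimate bias.

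The sample size is sound. Because the contradiction governs the headline estimate, it should be settled before any analysis.

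The survival rule is a separate, minor matter. Death precludes discontinuation, so it is a competing event, and censoring at admission discards follow-up that may still be observed. The hospitalisation example gives under 1 point per arm.

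**What to change.** - Reconcile 6.15.2, 6.15.4 and the Protocol Summary by making all enrolled patients, by arm, the primary set.
- Multiply impute missing 6-month status separately by arm from baseline covariates, 3-month PPI status and dispensing data. A recorded PPI sale may inform continued use; an absent sale must not be counted as discontinuation.
- Report complete-case and missing-as-still-on-PPI as sensitivity analyses. Imputation still assumes MAR, given more information, so the second is needed to show how far the result depends on it.
- Replace the sentence that MAR will be tested with a description of baseline differences between patients with and without 6-month data, by arm.
- For time to discontinuation, do not censor at hospitalisation patients who remain in follow-up, and treat death as a competing event.

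The cost is protocol and SAP wording and modest programming, using data the protocol already plans to collect for the primary outcome. The estimate may become less favourable. If every missing patient is counted as still on PPI, power with 111 per arm is 0.887 rather than 0.90.

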#### **6.15.5. Timing of analysis**

No interim analyses are planned. Analysis will take place after the last patient completed the 6-month assessment.

#### **6.15.6. Statistical software**

Data analysis will be performed using SAS and/or R software.

#### **6.16. Site monitoring**

Formal site monitoring will be performed by an CRA, and principal researcher related to data collection and intervention compliance. Researchers will also give previous training to the pharmacists and general practitioners to conduct the project according to the protocol.

## **6.17. Economic evaluation**

### **6.17.1. Overview**

Economic evaluation will be conducted alongside the non-randomized controlled trial, meaning the collection of costs and outcome data alongside the trial.

The economic evaluation will adopt an NHS perspective as base-case, including all health care resource use data and medicines costs, but also a broader perspective in a scenario analysis, including out-of-pocket expenses.

Data will be presented by costs parcel to allow alternative perspectives to be considered separately. The time horizon in the base-case analysis will be of 6 months.

### **6.17.2. Measurement and valuation of resources**

Health care resource use data will be based on patient-reported data. Data will be collected for the following period: baseline and 6-month follow-up. At baseline, information will cover the previous 6 months; at 6-month follow-up the service use since the previous time-point was recorded (baseline).

Resource-use information will be collected using questionnaires developed by the research team. The following resources, identified on literature (84,101) will be collected: regular medications used, number of doctor's appointments by type and setting (GP and specialist, public and private); number of emergency care episodes, number and major motive of hospitalizations, length of stay (LOS), number and type of diagnostic and therapeutic tests related with gastrointestinal symptoms.

For each item of service use reported in the resource use questionnaires, a unit cost will be applied and the total costs for each individual will be calculated. All unit costs will be for the most recent financial year over which the trial data will be collected and will be reported in Euros. Unit costs will be retrieved mostly from Portuguese official sources.

### **6.17.3. Intervention costs**

The cost of delivering the intervention to participants (e.g. training of pharmacy and FHU staff, number and type of GP's appointments, time spend by the pharmacist delivering the intervention alongside the time spent in preparing it, undertaking administrative or other miscellaneous tasks) is obtained from the research team, from the pharmacists records filled at each patient intervention point (Annex 10) and, from patient self-reported data collected during the telephone interview (e.g. GP appointment intervention related) compared against the information recorded by the GP on the "patient passport form" (Annex 9) and valued using established methods (102).

### **6.17.4. Outcomes for the economic evaluation**

#### **6.17.4.1. Primary outcome**

Cost-effectiveness will be explored in terms of the primary outcome measure (the proportion of patients who discontinued or decreased PPI dosage in the 6-month assessed by pharmacy medicine sales associated to the patients' tax information number (NIF) and confirmed by patient self-report).

#### **6.17.4.2. Health-related quality of Life**

The Health-Related Quality of Life (HRQoL) will be assessed using the EQ-5D-5L questionnaire applied at baseline and 6-month follow-up. The EQ-5D-5L is a generic preference-based measure of health state that covers five dimensions (mobility, self-care, usual activities, pain/discomfort, and anxiety/depression) that can be rated according to five levels of severity to define unique health states. The five-level version has showed increased reliability, sensitivity (discriminatory power) and feasibility compared to the previous three-level instrument. Participants are classified into one of 3125 health states, each associated with a score that can be used to calculate quality adjusted life years (QALYs) (103)

HRQoL weights for these health states have been previously elicited for the Portuguese population by Ferreira et al. (91,104). A score of 1 represents perfect health and a score of 0 represents death. The EQ-5D scores will be used to estimate patient-specific QALYs using the area under the curve method (105).

Mean QALYs measured by EQ-5D will be estimated using regression analysis to control for patients' covariates, including baseline EQ-5D score, (106) and will be used as a secondary outcome measure in the economic analysis.

#### **6.17.5. Cost and cost-effectiveness analysis**

Costs will be modelled with the most appropriate distribution for data. All analyses will be adjusted for pre-specified baseline characteristics, plus baseline costs.

Cost-effectiveness will be explored in terms of the primary outcome measure (reduction in PPI use) and QALYs and, will be assessed through the calculation of incremental cost-effectiveness ratios (ICER) – the additional cost of one intervention compared with another divided by the additional effects – using the net benefit approach (107). Cost-effectiveness acceptability curves will be presented by plotting the probability of the intervention being cost-effective for a range of possible values of willingness to pay for unit improvements in outcome (108). These curves are a recommended decision-making approach to dealing with the uncertainty that exists around the estimates of expected costs and expected effects associated with the interventions under investigation.

## 7. Study limitations

Methodologic limitations related to bias and confounding are inherent to the non-randomized design adopted in this study.

### Recruitment and selection bias

- The intervention FHUs were selected based on willingness to develop a collaborative intervention and may not represent a generalized sample of FHUs population.
- The pharmacies are also selected based on willingness to participate and may not represent a random sample from any well-defined population.
- Positive selection bias of patients: Strategies to minimize patient's self-selection will be adopted, namely a pop-up reminder at the pharmacy software whenever a PPI is dispensed during the recruitment period. We will also compare the characteristics between the patients who are approached and refused to participate in the study and the patients enrolled in the study.
- Some patients may be lost to follow-up during the study period. Depending on the volume of dropouts and missing data which may bias the data collection and the results, the baseline characteristics of this sub-group will be compared with the baseline characteristics of all patients recruited for the study per arm to assess any selection bias.
- To determine whether control allocation was effective descriptive statistics (means, proportions) will be calculated to assess the balance between the groups on important confounders such as age, sex, health status, baseline beliefs about medications and the burden of medicines. If such confounders are unbalanced between the groups, we will produce unadjusted and adjusted estimates of the primary and secondary outcomes.
- As General practitioner usual practices can also be a confounding domain, control patients were selected from the population served from FHUs in the control municipalities, with PPI prescription patterns similar to the interventions FHUs, defined by the volume of prescribed PPI per 1000 elderly ( $\geq 65$  y) in 2021, as FHU age pyramid.

### **Information bias**

- Self-reported medication taken and clinical information. It is believed that the patients are aware of the duration of exposure to a specific medication and clinical indication for its use as also of her/his co-morbidities. A pharmacist from the research team will interview the patients and this will help on the validation of the different medicines taken and co-morbidities.
- Recall bias (e.g., consumption of healthcare resources). Measuring health care consumption through patient's self-report can be associated with a recall bias, however, collecting data from clinical/hospital records is not feasible. Additionally, in cases as hospitalization or urgency visit, we do not expect patients not to remember if an impactful event like these occurred in the last 6 months.

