We intend, as part of the intervention, to be the pharmacist to collect all information regarding patients' medication profile. However due to the Covid-19 pandemic, the research team thought to reduce patient-community pharmacist face-to-face interaction time, and withdrawal from the pharmacist intervention package the task not directly related with the main PPIs' deprescribing and educational goals.

period, pharmacist will share the follow-up information with the GP using the established communication model. If any severe symptom is identified during this time span, pharmacists can send an urgent alert email to the FHU research coordinator. To assist the pharmacist through all intervention, a complete intervention log form, which include the telephone interview script (**Annex 10**), will be made available by the research team.

Patients can at any moment seek advice with community pharmacies and/or general practitioners. The overview of the multifaceted collaborative intervention package is depicted in Figure 2. intervention details are accessible on the C-SENIoR Intervention Flowchart (**Annex 11**).

[figure not shown]

**Figure 2** - Overview of the C-SENIoR multifaceted collaborative intervention package

The educational booklet was developed by the research team (pharmacists and general practitioners) for the study purpose. We performed a literature review of resources already tested in deprescribing interventions and available online (e.g., <https://deprescribing.org/>) and followed Fajardo et al recommendations (88) concerning readability of patient education materials for deprescribing interventions. The booklet is being tested with PPI elderly users, regarding its readability, dimension, key messages comprehension and images understanding.

This project will have the assistance of a clinical research associate (CRA) who will guarantee the information change flow foreseen between pharmacies and FHUs in the intervention arm.

Patients recruited from pharmacies assigned to the control group will receive usual care. For both groups, a baseline paper-based questionnaires will be delivered by the pharmacist (Annex 4), and three

telephone interviews, will be conducted by the research team at baseline, 3- and 6-month follow-up, respectively, to collect study data (see table 1).

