**Table 4 - Overview of data collection schedule and measurements**

| Time points / Data                                    | T0              | Ongoing (only intervention arm) | T1       | T2       |
|-------------------------------------------------------|-----------------|---------------------------------|----------|----------|
|                                                       | Recruitment - 0 | Intervention time span          | 3 months | 6 months |
| Socio-demographic and clinic characterization         | X               |                                 |          |          |
| Self-rated health status (SRH)(94)                    | X               |                                 |          |          |
| PPI specific outcomes                                 | X               |                                 | X        | X        |
| Other medication related outcomes                     | X               |                                 |          | X        |
| Quality of life (EQ-5D-5L)(90,91)                     | X               |                                 |          | X        |
| BMQ specific(92) applied to PPI                       | X               |                                 | X        |          |
| Adherence (MTA)                                       | X               |                                 |          | X        |
| Healthcare resource utilization (Economic Evaluation) | X               |                                 |          | X        |
| Intervention satisfaction questionnaire               |                 |                                 |          | X        |
| Process parameters                                    |                 | X                               |          |          |

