| Number of Adverse drug events                                                | 
 
• number
 
                                                                | Telephone interview                                | T0, T2 |
| Adverse drug events. Needed support from health professionals?               | 
 
• Yes
 
• No
 
                                                     | Telephone interview                                | T0, T2 |
| Healthcare resource utilization (within the last 6 months -T0 and T2) |                                                                                                                           |                                                    |        |
| Number GP's appointments all                                                 | 
 
• n GP appointments
 
                                                     | Telephone interview                                | T0, T2 |
| Number of Specialty practitioners' appointments                              | 
 
• n medical speciality health care appointments (ex. internal medicine)
 
 | Telephone interview                                | T0, T2 |
| Diagnostic tests or medical exams (gastric system related)                   | 
 
• Yes
 
• No
 
                                                     | Telephone interview                                | T0, T2 |
| Type of Diagnostic tests or medical exams (gastric system related)           | 
 
• To be defined
 
                                                         | Telephone interview                                | T0, T2 |
| Number Diagnostic tests or medical exams (gastric system related)            | 
 
• n diagnostic tests or exams
 
                                           | Telephone interview                                | T0, T2 |
| Diagnostic tests or medical exams with anesthesia                            | 
 
• n
 
                                                                     | Telephone interview                                | T0, T2 |

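### Follow-up health-care use is recalled once, over about 6 months, although both arms already receive a 3-month call at which it could be asked

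*Protocol*

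**What the plan says.** Section 6.17.2 fixes the source and the timing: "Health care resource use data will be based on patient-reported data", and "Data will be collected for the following period: baseline and 6-month follow-up". The follow-up question reaches back to baseline. Table 5 lists GP and specialist appointments, gastric tests, emergency visits, hospitalisations and out-of-pocket expenses as telephone items at T0 and T2 only, under the heading "Healthcare resource utilization (within the last 6 months -T0 and T2". In Table 4 the resource-use row is blank at 3 months.

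The contact schedule is wider than that. For both groups, section 6.5 states that "telephone interviews, will be conducted by the research team at baseline, 3- and 6-month follow-up". Section 6.7 confirms it for follow-up: "Study follow-ups include 2 telephone calls", one at 3 and one at 6 months. According to Table 4, the 3-month contact carries PPI outcomes and the BMQ. Section 6.8 lets follow-up data be collected up to a month before or after each time point.

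Section 7, under Information bias, concedes the weakness: "Measuring health care consumption through patient's self-report can be associated with a recall bias, however, collecting data from clinical/hospital records is not feasible". It adds that patients should remember a hospitalisation or an urgent visit. It says nothing about the less memorable items or about shortening the recall period.

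**The concern.** Section 7 treats recall bias as unavoidable because records cannot be used. Part of it is avoidable without records, since a call to every patient already takes place halfway through the window.

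Timing makes this matter. Section 6.5 plans GP contact 1 to 2 weeks after recruitment, with pharmacist calls 2 and 4 weeks after the GP reports the decision. Section 6.10 names symptom relapse as possible. Visits prompted by withdrawal would therefore fall mostly in the first half of the window, furthest from the only question about them.

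Cost-effectiveness is half of the stated aim. Incremental cost feeds the ICER and the acceptability curves in section 6.17.5. Adjusting for baseline costs, as planned there, cannot restore follow-up visits that were never reported.

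**Working it through.** The protocol states no recall rate, visit rate or incremental cost, so there is no figure of its own to reproduce. The sample-size calculation has no bearing on this point. What can be checked is the recall span, which items lack a second source, and how recall would behave under stated assumptions.

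**1. Recall span.** T2 is at month 6 with a 1-month tolerance either way, so recall back to baseline covers 5 to 7 months. The two descriptions of the T2 window agree only if the call is made exactly at month 6. At month 7, a question about the last 6 months covers months 1 to 7 and omits the first month, when withdrawal decisions are made. At month 5, it reaches one month back before recruitment. A question asked since baseline does neither.

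**2. Which items are exposed.**
- Intervention-related GP appointments: patient report compared with the GP's form (section 6.17.3; Table 5, ongoing paper form).
- Pharmacist time: intervention log (section 6.17.3, Table 5).
- Medicines: pharmacy software confirmed by interview (Table 5).
- Hospital stays and emergency visits: self-report only, which section 7 expects to be reliable.
- Unscheduled GP visits, specialist visits, gastric tests, out-of-pocket expenses: self-report only, with no second source and no defence in section 7.

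**3. Illustration with geometric forgetting.** Assumptions, not in the documents: an event is reported with probability r^e, where e is months elapsed; r is 0.97 to 0.85; early visits are spread evenly over months 0.75 to 2.5; calls are exactly on time. With the question at month c, the mean share reported is

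(r^(c - 2.5) - r^(c - 0.75)) / (1.75 × (-ln r)).

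For r = 0.90 and c = 6: (0.6916 - 0.5751) / (1.75 × 0.10536) = 0.63. For c = 3: (0.9487 - 0.7889) / (1.75 × 0.10536) = 0.87.

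| Monthly retention r | Early visits, T2 only | Early visits, T1 added | Visits in months 3 to 6, either schedule |
|---|---|---|---|
| 0.97 | 0.88 | 0.96 | 0.96 |
| 0.95 | 0.80 | 0.93 | 0.93 |
| 0.90 | 0.63 | 0.87 | 0.86 |
| 0.85 | 0.49 | 0.80 | 0.79 |

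**4. Illustration with linear forgetting.** Let recall fall in a straight line from 100% to r6 at 6 months: 1 - (1 - r6) × e/6, with r6 assumed to be 0.5 to 0.8. A visit 1.5 months after recruitment lies 4.5 months before T2 and 1.5 months before T1. At T2, recall is 1 - 0.5 × 0.75 = 0.625 to 1 - 0.2 × 0.75 = 0.85. At T1, it is 0.875 to 0.95. Both models show the same kind of gain.

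**5. Sign of the effect on incremental use** (geometric model, T2 only).
- One extra early visit, equal recall in both arms: counted as 0.88 to 0.49. Favours the intervention.
- One extra early visit offset by one fewer late visit (true net 0): counted as -0.08 to -0.30. Favours the intervention. With T1 added, it is counted as 0.00 to 0.01.
- One early visit saved: counted as -0.88 to -0.49, so the saving is understated. Runs against the intervention.
- Unequal recall, assuming 3 background visits per arm and 0.5 true extra early visits: r = 0.90 in both arms gives +0.32 (too low), but 0.94 in the intervention arm against 0.90 in control gives +0.66 (too high). The second result runs against the intervention.

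**The case against.** A reader might infer from the timing that incremental cost is simply biased towards the intervention. The documents do not support that. It would require net extra early visits, whereas section 6.10 expects relapses and complications to be uncommon and gives no rate. It would require no early savings, although pharmacist support and the resolution of drug interactions could replace some GP visits. It would also require similar recall in both arms. The arms are unblinded, and only the intervention arm has repeated pharmacist and GP contacts that might sharpen memory. Step 5 shows that the second and third conditions can each reverse the sign. This objection stands.

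It is also fair that the scheduled intervention contacts and the medicines have other sources, that out-of-pocket expenses enter only the scenario analysis, and that the shares above apply to an unknown and possibly small number of visits. No shift in euros or in the ICER can be shown. This stands too.

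Finally, section 7 discloses recall bias, and a 6-month recall is a design choice rather than an error. A two-part total depends on two successful calls, with 20% loss already expected (section 6.11). That is a real cost, but it can be handled by a simple rule. The disclosure does not settle the matter, because its two defences cover records and memorable events, not the shorter window that the existing call makes possible.

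**Conclusion.** The point holds as a cheap improvement. The schedule asks for follow-up resource use once, over 5 to 7 months, and leaves an existing contact in both arms unused for it. Early unscheduled GP visits, specialist visits, gastric tests and out-of-pocket expenses are likely to be under-counted.

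Under the assumed recall curves, adding a 3-month question raises the share of early visits reported from 0.49-0.88 to 0.80-0.96 (geometric), or from 0.625-0.85 to 0.875-0.95 (linear). These shares rest on assumed recall and timing. The direction of any bias in incremental cost is conditional, and its size cannot be derived from the protocol. The case for the change does not depend on the direction, because a shorter window reduces forgetting in both arms.

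**What to change.** In Tables 4 and 5, section 6.17.2 and the 3- and 6-month questionnaires (Annexes 13 and 14):

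- Ask the existing resource-use items at T1 for the period since recruitment and at T2 for the period since the T1 call. Sum the two for the 6-month total.
- Use that wording throughout in place of the two differing descriptions of the T2 window. The start of the window is then fixed whether T2 is early or late.
- If the T1 call is missed, ask at T2 since recruitment. If T2 is missed, keep the T1 data and handle the second half as missing data.
- Keep the 6-month recall at T0 as the baseline-cost covariate. It is an adjustment variable, so its window need not match.
- In section 7, limit the recall statement to what remains after this change.

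Cost: a few more questions in a call now planned at 10-15 minutes, small edits to two questionnaires, and some totals with one half missing. In return, first-half cost data are kept for patients lost between 3 and 6 months.
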